#### Secondary outcomes

1.The correlation between the Percentage of Glottic Opening (POGO) score and the difficulty of tracheal intubation.2.The impact of operator experience on VCI scale outcomes, including the influence of training level and prior videolaryngoscopy experience on interobserver agreement and VCI scoring.3.The incidence of tracheal intubation–related complications. While complications such as hypoxemia and laryngeal trauma are included as secondary outcomes, their expected low frequency means that related analyses will remain exploratory and descriptive in nature.

### Exploratory data

The study will collect essential data in the following domains (Table 1) (Appendix 3):1)Patient Demographics: Includes age, sex, weight, height, Body Mass Index (BMI), and ASA status.2)Operator Characteristics: Documents the experience of the intubator or observer categorized by role (resident or specialist), years of experience (< 4, 4–8, > 8), and the number of prior intubations with VL: < 25, 25–50, > 50.3)Procedure Setting: Documents the clinical environment, including operating theater, ICU, Post-Anesthesia Care Unit (PACU), or emergency department.4)Videolaryngoscope Characteristics: Captures the type of videolaryngoscope used during the procedure.5)Data Related to the VCI Scale: a) VCI score: Includes blade type (Macintosh or hyperangulated), POGO (categorized as < 25%, 25%–50%, 50%–75%, > 75%), and difficulty (easy, difficult, failed); b) Rescue Devices: If a rescue device is used, a new VCI score will be recorded.6)Complications: these include hypoxemia, esophageal intubation, dental injury, laryngeal trauma, bronchospasm or laryngospasm, and failed intubation.

**Table 1 tbl0001:** CRF VCISpain. VIDEO CLASSIFICATION OF INTUBATION VCISpain – Case Report Form (CRF).

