### Pre-data collection preparations

To ensure consistent and standardized application of the VCI scale across all centers, a comprehensive training and coordination strategy was implemented before the initiation of data collection. All participating anesthesiologists completed a structured, one-hour virtual training session led by the principal investigator ([name]) and study coordinators (PC, MV). The session included a detailed review of the study protocol, proper completion of the Case Report Form (CRF), and specific guidance on applying the VCI scale. Emphasis was placed on protocol adherence, data quality, and ethical considerations.

Each participating hospital received a complete study package containing the CRF, informed consent templates, and all necessary supporting documentation for protocol implementation. To ensure ongoing support, a dedicated online discussion forum was created to allow investigators to submit questions and receive timely clarifications. In addition, monthly virtual meetings are being held with all site investigators to reinforce protocol adherence, resolve methodological concerns, and ensure consistency in the interpretation and documentation of the VCI scale across centers.

All participating centers obtained approval from their ethics committees, ensuring compliance with applicable ethical and regulatory standards throughout the study.

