**Figure 2 fig0002:**
[figure not shown]
VCISpain (Video Classification of Intubation).

Simultaneously, a second anesthesiologist observes the tracheal intubation procedure and independently records the VCI score to assess interobserver reproducibility.

Complications will be prospectively recorded based on predefined clinical criteria, including:^25^ Hypoxemia (SpO_2_ < 90% for ≥ 10 seconds); Esophageal intubation (confirmed by capnography or clinical signs); Dental injury (visible tooth damage); Laryngeal trauma (presence of blood on the blade or tube, hoarseness, or stridor); Bronchospasm or laryngospasm (clinically diagnosed); Failed intubation (requiring a change in device or technique).

If a serious adverse event related to the videolaryngoscope is suspected, the attending physician may temporarily suspend the patient’s participation in the study. Throughout the process, patient safety is prioritized, and each center's standard protocols will be followed in the event of any incident.

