### Outcome measures

#### Primary outcome

The primary outcome is the inter-rater agreement and reproducibility of the VCI scale, defined as the level of concordance between the VCI scores assigned by the anesthesiologist performing the tracheal intubation and an independent observer.

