**Intubator Data**	
Role	Resident / Specialist
Years of experience	< 4 / 4–8 / > 8
Prior VL intubations	< 25 / 25–50 / > 50
Intubator VCI	
Blade type	Macintosh / Hyperangulated
POGO score	< 25% / 25–50% / 50–75% / > 75%
Ease of intubation	Easy / Difficult / Failed
If Difficult	Stylet / Bougie / Other adjunct
If Failed	Rescue device used + Rescue VCI

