### Statistical methods

A comprehensive statistical analysis will be conducted to describe the study’s quantitative and qualitative variables. Quantitative variables will be summarized using measures of central tendency and dispersion (mean ± standard deviation or median [interquartile range]), depending on the distribution of data. Qualitative variables will be presented as absolute frequencies and percentages.

To evaluate the interobserver reproducibility of the VCI scale among anesthesiologists, the Cohen’s Kappa coefficient will be used to measure the level of agreement between the anesthesiologist performing the tracheal intubation and the independent observer. Interpretation of agreement will follow standard criteria (≤ 0.20 poor, 0.21–0.40 fair, 0.41–0.60 moderate, 0.61–0.80 substantial, and > 0.80 almost perfect).

Binary logistic regression analysis will be performed to explore associations between key variables, specifically to assess the relationship between the Percentage of Glottic Opening (POGO) and the ease or difficulty of Tracheal Intubation (TI). Results will be reported as Odds Ratios (OR) with their corresponding 95% Confidence Intervals (95% CI).

Statistical significance will be determined using a p-value threshold of < 0.05. Data analyses will be performed using Stata 18 (StataCorp, College Station, TX, USA), a software providing advanced modeling and data-processing capabilities to ensure the precision and validity of the results.

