### Sample size

The study will enroll a total of 1,395 patients, accounting for a 5% dropout rate. The sample size calculation is based on achieving a precise estimate of the expected interobserver agreement measured by Cohen’s Kappa coefficient, assumed to be 0.80, with a desired precision of ± 0.11 and a confidence interval of 95%. Additionally, assuming a 10% incidence of difficult Tracheal Intubation (TI), this sample size will ensure adequate representation for meaningful secondary analyses.^6^ Patient recruitment is anticipated to take between 12 and 18 months, starting in September 2024.

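### The POGO bands overlap at exactly 50%, so two raters who see the same view can be recorded as disagreeing; the effect on the kappa depends on how often 50% is read

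*Protocol article*

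**What the plan says.** The section Exploratory data, item 5, gives the VCI score with "POGO (categorized as < 25%, 25%–50%, 50%–75%, > 75" per cent. Table 1, the CRF, prints "< 25% / 25–50% / 50–75% / > 75" per cent for the intubator and repeats it in the observer and rescue blocks. No field in the printed form holds the percentage itself.

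Under Primary outcome, the endpoint is "the level of concordance between the VCI scores assigned by the anesthesiologist performing the tracheal intubation and an independent observer". The text after Figure 2 says that "a second anesthesiologist observes the tracheal intubation procedure and independently records the VCI score". Under Statistical methods, Cohen's "Kappa coefficient will be used to measure the level of agreement" between the two; the article does not say whether kappa is taken on the whole score or per component, or whether it is weighted. The same section relates POGO to ease of intubation by binary logistic regression.

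The description of the VCI components fixes the moment at which POGO is read, but not where a reading of 50% goes. Under Pre-data collection preparations, training included "specific guidance on applying the VCI scale", without a stated rule for 50%.

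**The concern.** In an agreement study the recording form should not itself create disagreement. Here one of the three cut points belongs to two bands. The other two are clean: 25% falls only in the second band and 75% only in the third.

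The raters score independently, so they cannot settle a 50% view together. If they pick a band without a common rule, some identical readings enter the agreement table off the diagonal, and the result is charged to the scale. A larger sample does not remove this. Because only the band is kept, a ticked box cannot later be traced to 50% rather than, say, 30% or 70%. The same misplacement mixes the two middle POGO categories in the logistic regression.

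**Working it through.** **1. The plan's own figure, as a yardstick.** Under Sample size, kappa is "assumed to be 0.80, with a desired precision of ± 0.11 and a confidence interval of 95" per cent, with 10% difficult intubations, 5% dropout and a total of 1,395. For two raters and a binary trait, the large-sample variance of kappa times n is (1−k)[(1−k)(1−2k) + k(2−k)/(2p(1−p))]. With k = 0.80 and p = 0.10 this is 0.2 × [0.2 × (−0.6) + 0.96/0.18] = 1.0427.

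- Half-width 0.055: n = 1.0427 × (1.96/0.055)² ≈ 1,324.1, so 1,325; 1,325/0.95 gives 1,395, the stated total.
- Half-width 0.11, as written: n = 332, and 350 after dropout.

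The total therefore matches 0.11 as a full interval width. That is a separate matter. Here it supplies only a rough yardstick of ±0.055, because it refers to a binary trait and not to four POGO bands.

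**2. Model for the overlap.** These inputs are assumptions, because the article gives no POGO distribution and no share of views at 50%:

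- band shares b = 5/10/20/65%;
- kappa of 0.80 among the other views, so their table is 0.8·diag(b) + 0.2·b·bᵀ;
- a share s of views that both raters read as exactly 50%;
- under the overlap, each rater picks either middle band at random, so half of these pairs disagree;
- under a fixed rule, all of these pairs agree.

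Kappa = (Po − Pe)/(1 − Pe), unweighted.

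**3. Worked case, s = 5%.** Among the other views Pe = Σb² = 0.475 and Po = 0.8 + 0.2 × 0.475 = 0.895.

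- Overlap: Po = 0.95 × 0.895 + 0.025 = 0.8753. The marginals are 0.0475, 0.12, 0.215 and 0.6175, so Pe = 0.4442 and kappa = 0.4311/0.5558 = 0.776.
- 50% always in the lower band: Po = 0.9003, Pe = 0.4407, kappa = 0.822.
- 50% always in the upper band: Po = 0.9003, Pe = 0.4502, kappa = 0.819.

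**4. Results.**

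| Share at 50% | Fixed rule (lower / upper band) | Overlap | Loss |
|---|---|---|---|
| 1% | 0.805 / 0.804 | 0.795 | about 0.01 |
| 2% | 0.809 / 0.808 | 0.790 | about 0.02 |
| 5% | 0.822 / 0.819 | 0.776 | about 0.045 |
| 10% | 0.839 / 0.834 | 0.752 | about 0.085 |

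With flat (25% each) to very skewed (2/5/13/80%) bands, the loss is 0.03 to 0.06 at s = 5% and 0.07 to 0.11 at s = 10%. With otherwise perfect agreement and s = 10%, the overlap caps the unweighted kappa at 0.91; linear weights give 0.94 and quadratic weights 0.97.

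**5. Allowing rater error at 50%.** A simulation gave each rater a noisy reading of a common true view, rounded to steps of 5, 10 or 25 points, with error SD of 3, 6 or 10 points.

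- 5-point steps, SD 10: 0.486 / 0.495 under a fixed rule against 0.487 under the overlap, so almost no change.
- 10-point steps, SD 3: 0.838 / 0.848 against 0.800.
- 25-point steps, SD 3: 0.817 / 0.815 against 0.685, a loss of 0.13.

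The near-zero result needs both noise and fine steps. With 25-point steps the loss is still 0.07 at SD 10 (0.440 / 0.438 against 0.367).

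**The case against.** The strongest reply is that the size is wholly assumed. Nothing in the article shows that 50% is read often, and at 1–2% of views the loss is trivial. Of the assumed views, 30% lie in the two middle bands, so s = 10% is a high share. The model also has both raters reading the same 50% without error. That lifts the fixed-rule value above 0.80, so part of each loss in the table is a rise in the comparator. When one rater reads 50% and the other a neighbouring value, the overlap can even create agreement. All of this stands, and it limits the size.

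It also stands that training, the forum or the monthly meetings may have set a common convention, and that Figure 2 and Appendix 3 are not shown. With a shared convention there is no loss. The figures apply to an unweighted POGO-only kappa: kappas for blade type and ease would be untouched, and weighting would soften the effect.

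A reader might infer that the primary kappa is bound to be biased downward and pushed out of the almost-perfect class. The article does not support that. The planned 0.80 already lies in the substantial class (0.61–0.80), and the overlap values of 0.795 to 0.75 stay there. A class is crossed only if the starting or comparator value lies above 0.80. No success threshold is stated, so no decision turns on that boundary.

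What the reply does not remove is the overlap itself. The article prints the actual categories and the actual form, so this is a faulty stated rule and not a detail left to a fuller document.

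**Conclusion.** The concern holds in a conditional form, as something that should be fixed. The printed bands are not mutually exclusive at 50%, and the form does not keep what would be needed to repair this later. If raters lack a common convention, identical readings can be recorded as disagreement in one component of the primary outcome.

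Under the assumptions above, the loss in unweighted POGO kappa is about 0.01–0.02 when 1–2% of views are at 50%, about 0.045 at 5% and about 0.085 at 10%. Against the ±0.055 yardstick, the first is negligible, the second is close to it and the third exceeds it. Which case applies cannot be told from the article. The existence of the overlap is certain; its size is not. How far it reaches the primary result also depends on whether kappa is composite or per component, weighted or not.

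**What to change.** Assign 50% to one band only, in the Exploratory data section and in all three CRF blocks (intubator, observer, rescue), for example <25, 25–50, >50–75, >75. Leave the 25% and 75% cut points alone: they are already unambiguous, and moving 75% to the top band would add a second change of definition. Alternatively, record a whole-number POGO for each rater and derive these bands in REDCap. This would also show how often 50% is read.

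Issue the rule to all sites through the existing forum and monthly meetings. If training already set a convention for 50%, state it in the article.

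The cost is a small edit to the form and the database. Recruitment was planned to start in September 2024, so records collected on the present form cannot be re-banded. Keep them as recorded and report POGO agreement before and after the change as a sensitivity comparison. That comparison is not randomised and may also reflect growing familiarity with the scale.

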**General Information**	
Date	
Intubator’s e-mail	
Patient Demographics	
Age	
Sex/Gender	
ASA status	
Weight (kg)	
Height (cm)	
**Intubation Setting**	
Place of Intubation	Operating Room / ICU / Emergency / Other
**Videolaryngoscope Details**	
Videolaryngoscope Model	McGrath / C-MAC / Airtraq / Glidescope / Others
**Intubator Data**	
Role	Resident / Specialist
Years of experience	< 4 / 4–8 / > 8
Prior VL intubations	< 25 / 25–50 / > 50
Intubator VCI	
Blade type	Macintosh / Hyperangulated
POGO score	< 25% / 25–50% / 50–75% / > 75%
Ease of intubation	Easy / Difficult / Failed
If Difficult	Stylet / Bougie / Other adjunct
If Failed	Rescue device used + Rescue VCI
**Observer Data**	
Role	Resident / Specialist
Years of experience	< 4 / 4–8 / > 8
Prior VL intubations	< 25 / 25–50 / > 50
**Observer VCI**	
Blade type	Macintosh / Hyperangulated
POGO score	< 25% / 25–50% / 50–75% / > 75%
Ease of intubation	Easy / Difficult / Failed
If Difficult	Stylet / Bougie / Other adjunct
If Failed	Rescue device used + Rescue VCI
**Complications**	
Desaturation	< 92%
Esophageal intubation	Yes / No
Dental damage	Yes / No
Other	Specify
**Rescue VCI (If applicable)**	
Blade type	Macintosh / Hyperangulated
POGO score	< 25% / 25–50% / 50–75% / > 75%
Ease of intubation	Easy / Difficult / Failed

### Data collection and management

Data will be collected using a standardized and anonymized physical CRF, independently completed by both the intubating anesthesiologist and the observer during and immediately after the intubation procedure. The collected data will then be managed through the secure electronic platform Research Electronic Data Capture (REDCap), hosted at the University of Navarra (UNAV), ensuring stringent patient confidentiality and data integrity. REDCap offers validated data capture and a transparent audit trail through its comprehensive logging features.

### Data management workflow

Initial Data Capture: after each procedure, the anesthesiologist will complete the CRF, recording demographic data, procedure variables, and any observed complications.•Data Transfer to REDCap: the pseudo-anonymized data will be entered into the secure REDCap platform. Each patient will be assigned a unique encoding code that is not directly linked to their personal information, ensuring confidentiality.•Ethical and Regulatory Compliance: all data will be collected and stored in full compliance with Good Clinical Practice (GCP) guidelines and current data protection regulations.

### Data protection and quality assurance

Data Protection: the database will be encrypted and accessible only via individual passwords assigned to each investigator, ensuring robust security.•Protocol Supervision: a designated clinical investigator will oversee the implementation of the study protocol, thoroughly documenting any deviations, adverse events, or protocol violations.•Audits: the coordinating team and the principal investigator will conduct regular audits to verify data integrity and quality, maintaining high research standards.

### Data access and oversight

•Centralized Access: the principal investigator ([name]) and two coordinators (PC and MV) will manage centralized access to the data, ensuring supervision of data security, quality, and statistical analysis.•Access for Participating Centers: data will be made available to all participating centers to promote transparency and foster collaboration during analysis.•Centralized Oversight: the principal investigator will coordinate the processes of data collection, storage, and analysis.

### Statistical methods

A comprehensive statistical analysis will be conducted to describe the study’s quantitative and qualitative variables. Quantitative variables will be summarized using measures of central tendency and dispersion (mean ± standard deviation or median [interquartile range]), depending on the distribution of data. Qualitative variables will be presented as absolute frequencies and percentages.

To evaluate the interobserver reproducibility of the VCI scale among anesthesiologists, the Cohen’s Kappa coefficient will be used to measure the level of agreement between the anesthesiologist performing the tracheal intubation and the independent observer. Interpretation of agreement will follow standard criteria (≤ 0.20 poor, 0.21–0.40 fair, 0.41–0.60 moderate, 0.61–0.80 substantial, and > 0.80 almost perfect).

Binary logistic regression analysis will be performed to explore associations between key variables, specifically to assess the relationship between the Percentage of Glottic Opening (POGO) and the ease or difficulty of Tracheal Intubation (TI). Results will be reported as Odds Ratios (OR) with their corresponding 95% Confidence Intervals (95% CI).

Statistical significance will be determined using a p-value threshold of < 0.05. Data analyses will be performed using Stata 18 (StataCorp, College Station, TX, USA), a software providing advanced modeling and data-processing capabilities to ensure the precision and validity of the results.

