## Discussion

Airway management is a cornerstone of anesthetic practice; however, difficult tracheal intubation remains a significant concern, as highlighted by a recent audit in the United Kingdom.^6^ The introduction of VL has transformed airway management by providing superior glottic visualization, increasing first-attempt success rates, and reducing complications associated with multiple intubation attempts, such as hypoxemia, laryngeal trauma, and esophageal intubation.^25^ Nevertheless, the widespread adoption of VL continues to be limited by challenges related to training,^26^ financial constraints, and, notably, the lack of a standardized classification tool for documenting and communicating VL findings.^23^

The VCISpain study aims to bridge this gap by validating the VCI scale. This tool is designed to establish a standardized and reproducible language for airway management with videolaryngoscopy, addressing the limitations of traditional classification systems such as the Cormack-Lehane scale. Unlike these conventional tools, the VCI scale captures the unique features of videolaryngoscopy, particularly the “you see, and you fail” phenomenon, in which excellent glottic visualization does not necessarily ensure successful intubation.^17^ By standardizing communication, the VCI scale can enhance planning for future airway treatments, ultimately promoting patient safety.

The VCI scale integrates three key components: blade type (Macintosh or hyperangulated), the POGO score, and the ease or difficulty of the intubation procedure. This tool not only enhances documentation but also facilitates communication among clinicians, while supporting training and standardization in advanced airway management.

A previous study demonstrated the accuracy and reproducibility of the VCI scale in describing VL intubations.^22^ With its multicenter design ‒ encompassing 35 Spanish hospitals and anesthesiologists with varying levels of experience ‒ the VCISpain study provides a representative reflection of real-world clinical practice in Spain. Moreover, standardized training on the study protocol and the use of the VCI scale will help ensure the quality and reproducibility of the collected data.

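### Planned kappa precision and the named analyses make no stated allowance for clustering within 35 hospitals or repeated raters; a naive interval is too narrow if agreement is correlated within them

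*Protocol article*

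**What the plan says.** Everything here is from the protocol article.

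- **Statistical methods.** For the primary outcome, "the Cohen’s Kappa coefficient will be used to measure the level of agreement between the anesthesiologist performing the tracheal intubation and the independent observer". Associations, specifically between glottic view (POGO) and difficulty, go to binary logistic regression with odds ratios and 95% confidence intervals. No method is given for the kappa interval, and no hospital or rater term is mentioned.
- **Sample size.** "The study will enroll a total of 1,395 patients, accounting for a 5% dropout rate". That number is derived from the width of the kappa interval, with kappa taken as 0.80, precision written as ±0.11, 95% confidence and a 10% incidence of difficult intubation. No ICC or design effect is mentioned.
- **Discussion.** The study is described as "encompassing 35 Spanish hospitals and anesthesiologists with varying levels of experience". Differences among centres, devices and operators are listed as a limitation and then presented as a gain in external validity.
- **Secondary outcomes.** One is the influence of training level and prior videolaryngoscopy experience on agreement and scoring.
- **Table 1 (CRF).** General Information has a field "Intubator’s e-mail". The observer sections record role, years of experience, prior intubations and the VCI rating, but list no observer identifier.

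**The concern.** Each intubation yields a pair of ratings, and the pairs are grouped. Patients at one hospital share devices, local habits in using adjuncts, and probably raters. The ease component depends on adjunct use, and the device depends partly on what the centre has. So the chance that two raters agree may differ from hospital to hospital, or from rater to rater. Pairs from the same cluster then carry less information than the same number of unrelated pairs, and the usual standard error of kappa is too small.

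The study is sized entirely on the width of the kappa interval. What is at stake is therefore the honesty of that interval and the precision claimed for it. The operator-experience analyses are also exposed, because training and experience are largely constant across one rater's cases.

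**Working it through.** **Inputs.** From the Sample size section: kappa k = 0.80, prevalence p = 0.10, two-sided 95% (z = 1.96), 5% dropout, N = 1,395, precision ±0.11. From the Discussion: 35 hospitals. The ICC, the number of raters and the intubations per rater are not given, so they are assumed below and shown as ranges.

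**1. Reproduce the plan's figure.** For a binary rating with equal marginals, the large-sample variance of kappa times n is

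V = (1 − k)[(1 − k)(1 − 2k) + k(2 − k)/(2p(1 − p))]
= 0.2 × [0.2 × (−0.6) + 0.96/0.18]
= 0.2 × 5.2133 = 1.0427.

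Then n = 1.96² × V/h², where h is the half-width.

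- h = 0.055: n = 1,324.1, rounded up to 1,325; 1,325/0.95 gives 1,395. This matches exactly.
- h = 0.11, as printed: n = 331.02, rounded up to 332; 332/0.95 gives 350. This does not match.

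So 1,395 follows from the stated inputs if 0.11 is the full width of the interval, the pairs are independent and the design effect is 1. The figure of 1,325 evaluable pairs is derived, not printed.

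**2. Add hospital clustering.** Mean cluster size is m = 1,325/35 = 37.86. With equal hospitals:

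- design effect = 1 + (m − 1) × ICC = 1 + 36.86 × ICC;
- true half-width = 0.055 × √(design effect);
- coverage of a naive 95% interval = 2Φ(1.96/√(design effect)) − 1.

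| Assumed ICC | Design effect | Effective pairs | True half-width | Naive coverage |
|---|---|---|---|---|
| 0 | 1.00 | 1,325 | 0.055 | 95% |
| 0.01 | 1.37 | 968 | 0.064 | 91% |
| 0.02 | 1.74 | 763 | 0.072 | 86% |
| 0.05 | 2.84 | 466 | 0.093 | 75% |
| 0.10 | 4.69 | 283 | 0.119 | 63% |

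**3. Find where the printed ±0.11 fails.** Solve 0.055 × √(1 + 36.86 × ICC) = 0.11. The design effect must reach 4, so ICC = 3/36.86, about 0.08. If hospital sizes vary with an assumed coefficient of variation of 0.65, the limit falls to about 0.06.

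**4. Rater-level clusters.** With an assumed 5 to 20 intubations per rater and ICC 0.05 to 0.20, the design effect runs from 1.2 to 4.8 and the half-width from 0.060 to about 0.12.

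**5. Check by simulation (35 hospitals × 38 pairs).** When both prevalence and the disagreement rate varied by hospital, the true variance of kappa was 1.6 to 3.8 times the naive variance, and coverage was 87% down to 69%. When disagreement did not vary by hospital, the ratio was about 1.1.

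**6. Logistic model for POGO.** POGO varies between patients within a hospital. At an outcome ICC of 0.10 the simulated variance ratio for its coefficient was about 0.9 to 1.2. It reached 1.6 only when the ICCs of outcome and POGO were both 0.20.

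**The case against.** The best defence is that the article is silent rather than wrong. It names kappa as the estimator and never says that pairs will be treated as independent. An unseen analysis plan may specify clustered intervals. That stands for the analysis, so a reader should not infer that the plan declares independence. It does not dispose of the sample size, which is fixed in the article with no clustering allowance mentioned.

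One can also note that halving a half-width multiplies n by four, so ±0.11 with a design effect of 4 would give the same 1,395. Arithmetic alone cannot exclude this. But no design effect or ICC is stated, and the full-width reading needs only a slip of notation.

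Four stronger readings are tempting and should be resisted.

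- **The interval will certainly be too narrow.** This depends on an ICC that the article does not give, and the simulation shows little loss if disagreement does not vary by hospital. Repeated raters are likely, but their number is not stated.
- **The scale may be put in too high an agreement band.** The bands are applied to kappa itself, with no rule on a confidence limit. Clustered intervals leave the estimate and its band unchanged.
- **The odds ratios suffer equally.** For POGO they hardly do, as step 6 shows.
- **Observer identity is lost for good.** Table 1 lists no observer ID, but the full form (Appendix 3) is not shown, both raters complete the form, and original records are kept at the centres.

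**Conclusion.** The point holds in conditional form. The sample size reproduces with no design effect, and the text names only plain kappa and plain logistic regression, despite 35 hospitals and heterogeneity that the article itself acknowledges. If agreement is correlated within hospital or rater, a naive kappa interval will understate the uncertainty. Even an ICC of 0.01 lowers coverage to about 91%, and 0.05 lowers it to about 75%. These figures rest on assumed ICCs, equal hospital sizes, and a simple design effect applied to kappa for a binary rating.

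The study is not shown to be too small for its printed target: ±0.11 survives up to a hospital ICC of about 0.08. What is exposed is the reported interval for kappa and the analyses of operator experience, not the kappa estimate, its band or, to any great extent, the POGO odds ratio.

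**What to change.** 1. Compute the kappa confidence interval by bootstrap, resampling whole hospitals. This also absorbs rater-level correlation as long as raters stay within one hospital, and it needs no observer ID. Add rater-level clustering as a sensitivity analysis.
2. Use hospital- or rater-clustered standard errors, or a random intercept, in the regression models. Give priority to the operator-experience analyses.
3. Confirm that the full CRF carries a coded observer ID, and add one if it does not. Recruitment was due to start in September 2024, so this should be settled promptly.
4. State in the Sample size section that the planned precision assumes independent pairs, and give the half-widths for the range of ICCs above. Correct or explain ±0.11 at the same time, since the stated inputs give 350 patients for that half-width without a design effect.

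The cost is a few lines of Stata, at most one CRF field, and wider reported intervals. No extra patients are needed.
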